**Figure 2 figure2:**

A framework for building predictive models using patient, physician profile, and environmental variable features.

###### Data Preprocessing

We will use established techniques, such as imputation, to deal with missing values and detect and remove/correct invalid values [48,60]. For environmental variables, we will use standard methods [61,62] to obtain aggregate values, such as monthly averages, from raw values. For administrative and clinical attributes, we will use grouper models such as the Diagnostic Cost Groups system to group diseases, procedures, and drugs, and reduce features [13,25].

###### Patient Features

We will use standard patient features, such as age and diagnoses, that have been studied in the clinical predictive modeling literature [13,27,48]. Commonly used features are listed in Luo [32] and Schatz et al [29].

###### Physician Profile Features

Some physician profile features are computed using only physician practice profile attributes. Examples of such features are (1) the logarithm of the normalized number of a physician’s patients with a specific characteristic, such as a specific disease, gender, race, or age range (a logarithm is used to diminish the difference in the number across physicians); (2) the logarithm of the number of specific procedures performed by a physician; (3) the mean outcome of a physician’s patients with a specific disease (if a physician does not have enough patients with a specific disease, we will set the disease’s mean outcome in the physician’s practice profile to the mean outcome of all patients with the disease); (4) the average cost of a physician’s patients with a specific disease; (5) the average ratio of chronic controller to total asthma medications of a physician’s asthma patients, which is an asthma care quality measure [63-66]; (6) the mean of a feature of a physician’s (pediatric) asthma patients with desirable/undesirable outcomes; (7) a physician’s age; (8) a physician’s total office hours per week; (9) a physician’s years in practice; and (10) a physician’s specialty.

Some physician profile features are formed by combining patient and physician practice profile attributes, characterizing the match of patient and physician. Examples of such features are (1) the distance between the physician’s office and patient’s home, (2) an indicator of whether the physician and patient are of the same gender [67], (3) an indicator of whether the physician and patient speak the same language, and (4) an indicator of whether the physician accepts the patient’s insurance.

The preceding lists of physician profile features are only for illustration purposes and are by no means exhaustive. More physician profile features will be investigated in this study. When a patient is managed by multiple physicians simultaneously, the patient’s outcomes are affected by the profile features of all these physicians. A traditional method for handling this situation is to use episode grouper software to split the whole span of patient care into episodes and assign each episode to a single physician [13,68]. An episode of care is “a series of temporally contiguous health care services related to treatment of a given spell of illness or provided in response to a specific request by the patient or other relevant entity” [27,69]. Apart from the episode method, we will investigate other methods to combine multiple physicians’ profile features.

###### Environmental Variable Features

We will use standard environmental variable features such as monthly averages from clinical predictive modeling literature [57].

###### Definition of Asthma Cases and Outcomes

As test cases, we will focus on primary care physicians and develop and test our idea using (1) pediatric asthma and (2) adult asthma. The method described in Schatz et al [29,70,71] will be used to identify asthma patients. A patient is considered to have asthma if he/she has (1) at least one *International Classification of Diseases, Ninth Revision* (*ICD-9*) diagnosis code of asthma (493.xx) or (2) at least 2 asthma-related medication dispensing records (excluding oral steroids) in a 1-year period, including inhaled steroids, beta-agonists (excluding oral terbutaline), oral leukotriene modifiers, and other inhaled antiinflammatory drugs [29]. We will use 2 outcome measures for asthma: (1) primary outcome—whether acute care (inpatient stay, urgent care, and emergency department visit) with a primary diagnosis of asthma (*ICD-9* code: 493.xx) occurred for a patient in the following year [28,29,31,32,56,72,73] and (2) secondary outcome—the total amount of reliever medication and oral steroid medication for acute asthma exacerbations that a patient refilled in the following year. Total refill amount reflects the number and degree of asthma exacerbations experienced by the patient [63,64] and is available in our dataset.

###### Predictive Models

We will use Weka [74], a widely used open-source machine learning and data mining toolkit, to build predictive models. Weka integrates an extensive set of popular machine learning algorithms, ensemble techniques combining multiple predictive models, feature selection techniques, and methods for handling the imbalanced class problem. Both numerical and categorical variables appear in clinical, administrative, and environmental data. We will use supervised algorithms that can handle both types of variables, such as decision tree and *k*-Nearest Neighbor. We will test every applicable algorithm and manually tune hyperparameters.

The accuracy achieved by state-of-the-art predictive models is usually far below 80% [28,29]. We would regard Aim 1a (to build predictive models for individual patient health outcomes) partially successful if we can improve accuracy by 10% or more for either pediatric or adult asthma. We would regard Aim 1a completely successful if we can improve accuracy by 10% or more for both pediatric and adult asthma. Given a set of features, we will use 3 methods to improve model accuracy. First, some features are unimportant or highly correlated with one another, which may degrade model accuracy. To address this, we will use standard feature selection techniques, such as the information gain method, to identify important features that will be used in the model [28,42,74]. Second, for a categorical outcome variable with 2 values, the corresponding 2 classes in our dataset can be imbalanced, meaning many more instances exist for one class than the other. This can potentially degrade model accuracy. We will use standard techniques such as Synthetic Minority Oversampling Technique (SMOTE) to address this [74]. Third, we will try ensemble techniques, such as random forest, that combine multiple models and usually work better than individual models [74].

###### Accuracy Evaluation and Sample Size Justification

We have 11 years’ data. We will use a standard approach to train and test predictive models. We will conduct stratified 10-fold cross validation [74] on the first 10 years’ data to train and estimate the accuracy of models. The 11th year’s data will be used to assess the best models’ performance reflecting use in practice. For categorical outcome variables, we will use the standard performance metric of the area under the curve (AUC) of the ROC [74] to select the best model. For continuous outcome variables, we will use the standard performance metric of *R*
^
*2*
^ to select the best model and also report the Cumming’s prediction measure (equivalent to the mean absolute prediction error) [25,32]. To determine the clinical, administrative, and environmental variable attributes essential for high accuracy, backward elimination [48] will be used to drop independent variables as long as the accuracy does not drop by more than 0.02.

We will test the hypothesis that adding physician profile features can increase prediction accuracy twice—once for children and once for adults. We will compare the accuracies achieved by 2 predictive models using the best machine learning algorithm. The first model will use patient, physician profile, and environmental variable features; the second, only patient and environmental variable features. We will accept the hypothesis if the first model achieves higher accuracy (AUC or *R*
^
*2*
^) than the second model by 10% or more.

Consider the categorical outcome variable of acute care usage with 2 values (classes). A predictive model using only patient and environmental variable features usually achieves an AUC far less than 0.8 [28,29]. Using a 2-sided *z* test at a significance level of .05 and assuming for both classes a correlation coefficient of .6 between the 2 models’ prediction results, a sample size of 137 instances per class has 90% power to detect a difference of 0.1 in AUC between the 2 models. The 11th year’s data include approximately 27,000 children and 75,000 adults with asthma, providing adequate power for testing our hypothesis. To train a predictive model well, typically the ratio of the number of data instances to the number of features should be 10 or more. In our case, a few hundred features at most will be used; thus, our dataset would be large enough for training the predictive models. The case with the continuous outcome variable is similar (see Aim 1b: Sample Size Justification).

#### Aim 1b: Build Predictive Models for Individual Patient Costs.

We will use an approach similar to that in Aim 1a, but change the prediction target from health outcomes to individual patients’ total costs in the following year [13,25,27]. Each medical claim is associated with a billed cost, an Intermountain Healthcare internal cost, and a reimbursed cost [13]. We will use the Intermountain Healthcare internal cost [33], which is less subject to variation due to member cost-sharing [13], and reflects actual cost more closely. To address inflation, we will standardize all costs to 2014 US dollars using the medical consumer price index [75].

In addition to the rare use of physician profile features, 2 other major reasons also cause low accuracy in predicting an individual’s cost. First, most existing work on predicting costs uses linear regression models [13,25,27]. In reality, costs do not follow a linear model [26]. Second, the cost of a patient with a specific disease is the cost of treating all his/her diseases [25]. To consider this factor, each model uses many features or independent variables (eg, one feature per disease) and can easily have insufficient training data [48]. To address these 2 problems, we will try nonlinear, disease-specific, machine learning models, which were proposed in a previous paper [32], but have not been implemented so far. This method’s key idea is to reduce features by merging several less important features into one feature while maintaining important features as separate. The current approach of identifying important features and grouping other features is manual. We will also investigate automatic approaches. For example, we can regard the top features with the largest associations with the outcome variable as important ones. The remaining features are clustered using a similarity metric to form groups. The automatic approach is general and can be used to improve prediction accuracy of any continuous outcome variable that has a complex nonlinear relationship with many independent variables.

##### Sample Size Justification

In predicting an individual’s cost, a predictive model using only patient and environmental variable features usually achieves an *R*
^
*2*
^ <20% [26]. Using an *F* test at a significance level of .05 and assuming the presence of 70 patient and environmental variable features, a sample size of 245 patients has 90% power to detect an increase of 10% in *R*
^
*2*
^ attributed to 30 physician profile features. The 11th year’s data include approximately 27,000 children and 75,000 adults with asthma, providing adequate power for testing our hypothesis of an increase of 10% or more in *R*
^
*2*
^.

Our goal is to achieve a 10% or more improvement in accuracy. If our models cannot achieve high accuracy on the entire group of asthma patients, we will build separate models for different subgroups of asthma patients. Patient subgroups are defined by specific characteristics, such as age, prematurity, comorbidity, or insurance type that are usually independent variables of the original models. If our models still cannot achieve high accuracy, we will conduct subanalyses to identify patient subgroups on which our models perform well. In this case, our final models will be applied only to the identified patient subgroups.

A missing data problem occurs when a patient has several physicians belonging to different provider groups, with no single provider having complete information on the patient. We anticipate that adding physician profile features can improve prediction accuracy even if some data are missing. The missing data problem is unlikely to be an issue for children in our case, as Intermountain Healthcare provides approximately 85% of pediatric care in Utah [52]. If the Intermountain Healthcare EDW misses too much data for adults, we will use claim data in the all-payer claims database [76] to compensate. In the future when applying our predictive models to other health care systems, this compensation strategy can be used. Also, we expect missing data problems to be uncommon in health maintenance organization settings where all physicians managing the patient belong to the same provider group and the provider’s electronic medical record and administrative systems usually have all medical data collected on the patient [77].

As mentioned previously, identifying asthma requires medication order and refill information. Our dataset includes this information because Intermountain Healthcare has its own health insurance plan (SelectHealth [78]). If the Intermountain Healthcare EDW is missing too much refill information, we will use claim data in the all-payer claims database [76] to compensate. If adding physician profile features cannot significantly increase prediction accuracy for asthma, we will choose chronic obstructive pulmonary disease or heart diseases for Aims 1 to 4.

We have a large dataset. If we experience scalability issues using Weka, we will use a parallel machine learning toolkit, such as Spark’s MLlib [79-81], to build predictive models on a secure computer cluster available to us at the University of Utah Center for High Performance Computing [82].

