#### Summary Statistics of the Dataset

Our contracted Intermountain Healthcare data analyst will execute Oracle database SQL queries to extract a deidentified version of the dataset, encrypt it, and transfer it securely to a password-protected and encrypted computer on which we will perform secondary analyses. Intermountain Healthcare uses dedicated tables to track changes in diagnosis and procedure codes over time. The dataset contains information on patient encounters over the past 11 years. For the last 5 years, data captured for children cover more than 400 pediatric primary care physicians, 360,698 pediatric patients (age zero to 17 years), and 1,557,713 clinical encounters per year. Data captured for adults cover more than 600 primary care physicians, 878,448 adult patients (age ≥18 years), and 5,786,414 clinical encounters per year. Asthma prevalence is approximately 7.6% in the Intermountain Healthcare pediatric population and approximately 8.6% in the Intermountain Healthcare adult population. The dataset includes approximately 400 attributes and represents electronic documentation of approximately 85% of pediatric care and approximately 60% of adult care delivered in Utah [33,52]. Intermountain Healthcare dedicates extensive resources to data accuracy and integrity. Due to its large size and attribute richness, the dataset gives us many advantages for exploring the proposed predictive models.

In addition, we will use 21 environmental variables recorded over 11 years by regional monitoring stations within the geographic area covered by Intermountain Healthcare. These variables include particulate matter up to 2.5 μm in size (PM_2.5_) and 10 μm in size (PM_10_), carbon monoxide (CO), nitrogen dioxide (NO_2_), sulfur dioxide (SO_2_), ozone (O_3_), temperature, relative humidity, wind speed, precipitation, dew point, and activities of viruses (adenovirus; enterovirus; human metapneumovirus; influenza A virus; influenza B virus; parainfluenza virus types 1, 2, and 3; rhinovirus; and respiratory syncytial virus). Because the monitoring stations are spread across a large geographic area including the entire state of Utah, the readings of the same environmental variable can differ greatly at different monitoring stations at any time.

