#### Outcome Evaluation and Sample Size Justification

We will compare outcomes achieved by 2 predictive models using the best machine learning algorithm. The first model will use patient, physician profile, and environmental variable features; the second only patient and environmental variable features. We will test 3 hypotheses: adding physician profile features will be associated with reduced (1) costs, (2) hospital admissions, and (3) emergency department visits. We will test each hypothesis twice, once for children and once for adults. Cost data will be log-transformed due to skewed distribution [13]. We will accept the primary hypothesis if the first model can reduce the log cost by 10% multiplied by its standard deviation compared with the second model. One-sided paired-sample *t* test will be used to test the difference in log cost between the 2 models’ outcomes. McNemar’s test will be used to test the difference in hospital admissions and emergency department visits. At a significance level of .05, a sample size of 857 instances has 90% power to confirm the primary hypothesis. The 11th year’s data include approximately 27,000 children and 75,000 adults with asthma, providing adequate power for testing the primary hypothesis.

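### Patient-level tests ignore clustering by physician, so the McNemar and log-cost p values are too optimistic, and the R² F test sizes a linear model that the plan does not use

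*Protocol article*

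**What the plan says.** The question in Aims 1 and 4 is whether physician profile features add value to a model that already has patient and environmental features. The protocol article names four tests:

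- **Aim 1a, Accuracy Evaluation and Sample Size Justification:** a two-sided z test for AUC, with 137 instances per class.
- **Aim 1b, Sample Size Justification:** an F test for R², "assuming the presence of 70 patient and environmental variable features, a sample size of 245 patients has 90% power" for a 10% gain in R² "attributed to 30 physician profile features".
- **Aim 4, Outcome Evaluation and Sample Size Justification:** a one-sided paired t "test will be used to test the difference in log cost between the 2 models", with 857 instances.
- **The same Aim 4 section:** McNemar's test for hospital admissions and emergency department visits.

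Adequacy is argued each time from about 27,000 children and 75,000 adults. The article does not mention clustering by physician.

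Under Summary Statistics of the Dataset, "data captured for children cover more than 400 pediatric primary care physicians" and "Data captured for adults cover more than 600 primary care physicians". Under Physician Profile Features, one group of features is computed from the physician's profile alone (for example age, specialty and years in practice). A second group describes the match of patient and physician.

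On model form, Aim 1b states: "In reality, costs do not follow a linear model". It plans nonlinear machine learning, and Aim 1a assesses the best models on the 11th year's data.

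**The concern.** A feature that takes one value for all patients of a physician shifts their predictions together. The difference between the models with and without such features is then likely to be correlated among patients of the same physician. A test that counts every patient as independent understates the standard error of that difference.

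At stake are the p values and intervals reported for the added value of physician features. They matter most where a p value alone would carry the conclusion:

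- the McNemar tests, for which Aim 4 states no margin;
- the log-cost p value as reported;
- the rule in Aim 1b to move all aims to another disease if accuracy does not rise significantly, if that is judged by a patient-level test.

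The second problem needs no assumption about correlation. The F test for an R² increment belongs to nested linear regressions fitted and assessed on the same data. A difference in held-out R² between two machine learning models does not follow that distribution, and can even be negative.

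**Working it through.** **1. The plan's own figures.**

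- F test inputs (Aim 1b): alpha .05, 70 control and 30 tested features, R² gain 0.10. Base R² is given as below 20%; 0.20 is used. f² = 0.10/(1 − 0.20 − 0.10) = 0.1429; λ = 245 × 0.1429 = 35.0; df = 30 and 245 − 101 = 144. Power is 0.9001, and 245 is the smallest N reaching 0.90. The figure is correct, as a calculation for linear regression with independent patients.
- Reading the 10% as relative (0.20 to 0.22) would need 1,209 patients, so 245 implies an absolute gain of 0.10.
- Paired t: ((1.645 + 1.282)/0.1)² = 856.4, rounded up to 857. This takes the 0.1 SD as the SD of the paired difference, with independent patients.

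**2. Patients per physician.** 27,000/400 = 67.5 and 75,000/600 = 125. The physician counts are lower bounds, so these averages are upper limits.

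**3. Design effect and true error.** The ICC of the paired difference is not in the document; 0.01 to 0.05 is assumed. DE = 1 + (m − 1) × ICC. Two-sided error = 2 × [1 − Φ(1.96/√DE)]; one-sided error = 1 − Φ(1.645/√DE).

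| | ICC | DE | Two-sided 5% test | One-sided 5% test |
|---|---|---|---|---|
| Children | 0.01 | 1.67 | 12.9% | 10.1% |
| Children | 0.05 | 4.33 | 34.6% | 21.4% |
| Adults | 0.01 | 2.24 | 19.0% | 13.6% |
| Adults | 0.05 | 7.20 | 46.5% | 27.0% |

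**4. The F test under clustering.** A partial F test in a linear model with 30 pure-noise physician-level features was simulated, 300 runs per setting. It rejected in 5% of runs at an outcome ICC of 0. At 0.01 it rejected in 68% (400 physicians × 68 patients) and 94% (600 × 125). Even at an ICC of 0.10, the largest R² gain from noise was about 0.019.

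**5. Do the margins protect the main decisions?**

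- *Aim 4 primary.* At the largest design effects above, effective n is 27,000/4.325 = 6,243 and 75,000/7.20 = 10,417. A difference of 0.1 SD is then 0.1 × √6,243 = 7.9 and 0.1 × √10,417 = 10.2 standard errors from zero.
- *Aim 1, R².* The margin of 0.10 is about five times the largest noise gain in step 4.
- *Aim 1, AUC.* With 137 independent instances per class, a difference of 0.1 is 1.96 + 1.28 = 3.24 standard errors. To keep that distance needs about 137 × 4.33 = 593 children and 137 × 7.20 = 986 adults with an event: 2.2% and 1.3% of patients. The event rate is not in the document.

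**6. Power.** For ICC 0.01 to 0.05, 857 becomes 1,427 to 3,707 (children) and 1,920 to 6,170 (adults); 245 becomes 408 to 1,060 and 549 to 1,764. All are far below 27,000 and 75,000.

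**The case against.** The strongest reply is that the main decisions do not rest on p values. Aim 1 accepts its hypothesis on a gain of 10% or more, and the z and F tests appear only in the sample size text. The Aim 4 primary hypothesis requires a log-cost reduction of 0.1 SD. This stands: a reader might infer that physician features would be falsely declared useful in 13% to 47% of cases, but those rates describe rejection at the 5% level and not acceptance under the margin rules.

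It is also fair that the ICC is assumed. The document supports only its direction: the introduction calls physician characteristics influential and reports large practice variation. Nor is it right to treat physicians as the only independent units. The match features (such as distance or same gender) vary within a physician, and Physician Profile Features notes that a patient may have several physicians at once.

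Finally, this is a condensed article, and variance estimation for AUC and R² is commonly left to an analysis plan. That covers the Aim 1 intervals. It does not cover the paired t and McNemar tests, which the article itself fixes as the analyses.

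**Conclusion.** The point holds in a limited form. The named tests treat patients as independent although many tested features are constant within a physician. Under positive within-physician correlation of the paired differences, p values are too small and intervals too narrow. The size, a design effect of 1.7 to 4.3 in children and 2.2 to 7.2 in adults, rests on the assumed ICC and on upper-limit cluster sizes. The consequence falls on the McNemar tests, the reported log-cost p value, and any significance test used for the disease switch (the article names none for it).

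The document does not support a reading that the study is underpowered, that 245 is miscalculated, or that the margin-based conclusions are unsafe. The last of these takes the 10% as absolute and the 0.1 SD as that of the paired difference, as the plan's own sample sizes do. For AUC it also needs event rates above roughly 1% to 2%.

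The mismatch of the F test is a separate and smaller error. It justifies the sample size with a model form that Aim 1b itself rejects, but it does not threaten adequacy at 27,000 and 75,000 patients.

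**What to change.** - On the 11th-year data, replace the patient-level paired t and McNemar tests by a physician-cluster bootstrap. Assign each patient to the one primary care physician listed in the record, resample physicians with all their patients, and use at least 2,000 replicates.
- Report the confidence interval and p value from it for the differences in AUC, held-out R², log cost, and admission and emergency-visit rates. Use the same method for any significance test behind the disease switch.
- Keep the margin rules and the log-cost endpoint.
- Drop the F-test sizing in Aim 1b, or label it a linear-model approximation. State all sample sizes with an assumed design effect.
- Say that these intervals reflect variation among physicians within this health system. They do not by themselves support use in other systems.

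The cost is computing time, some rewording and wider intervals. No new data are needed.
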